## Methods: participants, interventions, and outcomes

### Study setting {9}

The present study will be conducted across multiple settings corresponding to the sequential three phases of the research.i.Phase one will be conducted through a narrative literature review, expert consultations (involving EMDR therapists) based in Pakistan. These activities will be carried out through a combination of in-person meetings and secure online platforms, depending on participant availability.ii.Phase two will be implemented in both online and in-person clinical settings at the selected clinics or psychotherapy centers located in the three selected cities in Pakistan, where the adapted DeprEnd EMDR therapy protocol will be delivered by four EMDR certified therapists. Data collection during this phase will occur through clinical assessments and standardized self-report measures.iii.Finally, phase three will be conducted as a multi-center randomized controlled trial study implemented in both online and in-person clinical settings at the selected clinics or psychotherapy centers located in the three selected cities in Pakistan, where the adapted DeprEnd EMDR therapy protocol will be delivered by four EMDR certified therapists. Data collection during this phase will occur through clinical assessments and standardized self-report measures. During this phase, process fidelity and adherence to the adapted DeprEnd EMDR protocol will be monitored at mid of therapy. 

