### Implementation {16c}

Following eligibility confirmation and baseline assessments (T_1_), randomization will be executed through the designated electronic platform (OpenClinica/Sealed Envelope) by a research assistant who will not be involved in outcome measurement. The online system will be connected to the therapists’ and patients’ emails. It will automatically notify the treating therapist of the allocated intervention mode (online or in-person) and inform the patient via secure messaging, while maintaining the blinding of outcome assessors. To ensure protocol fidelity, therapists will receive arm-specific procedure checklists corresponding to their notification. The principal investigator will conduct weekly cross-checks between the electronic allocation records and physical randomization documents to detect and rectify any discrepancies.

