## Assignment of interventions: blinding

### Who will be blinded {17a}

Due to the single blind-nature of intervention, complete blinding is not feasible for clients or therapists regarding delivery mode (online vs. in-person EMDR). However, therapists will remain blind until after completing the initial consultation with clients. Outcome assessors (research assistants) and data analysts will maintain full blinding throughout the trial. To minimize bias:Outcome assessors will perform clinical evaluations before therapy sessions begin and without access to subsequent treatment setting information.Data analysts will work with de-identified datasets using group codes.For fidelity analysis, independent reviewers will assess edited audio/video recordings with all platform-specific references removed.Blinding success will be empirically evaluated at the study midpoint by asking blinded personnel to guess group allocations, with ≤ 60% correct guesses indicating adequate maintenance of blinding.

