## Statistical methods

### Statistical methods for primary and secondary outcomes {20a}

All quantitative analyses in Phase two and Phase three will be conducted using appropriate statistical methods aligned with the study design, outcome structure, and hypotheses. Analyses will be performed using standard statistical software (e.g., SPSS and Python 3.10+, standard statistical libraries). Phase two analyses will focus on feasibility, acceptability, safety, and preliminary symptoms change following delivery of the culturally adapted DeprEnd EMDR protocol. Feasibility indicators will be summarized using descriptive statistics, and a one-sample t-test with 95% confidence intervals and significance levels. Repeated-measures General Linear Models will be used to determine temporal symptoms changes. These analyses will be exploratory and will not be intended to establish definitive clinical effectiveness.

Phase three analyses will be conducted within a randomized controlled trial framework. First, non-inferiority is evaluated by comparing the estimated 95% confidence interval for the between-group difference to a pre-specified margin; if the upper bound lies entirely below the margin, non-inferiority is concluded [81]. For the primary outcome, non-inferiority is based on the between-group difference in change scores on the Hamilton Depression Rating Scale-17 from baseline (T1) to the end of treatment (T3), calculated as online EMDR minus in-person EMDR. A non-inferiority margin (δ) of 3 points was pre-specified a priori, consistent with previously published non-inferiority trials that defined margins on this scale [82]. For secondary outcomes of anxiety, as assessed by the Generalized Anxiety Disorder-7, between-group differences in change scores will be examined using analogous comparative principles and reported with effect estimates and confidence intervals. A non-inferiority margin (δ) of approximately 2.5 points on this scale was pre-specified a priori, informed by clinically meaningful score differences used in prior non-inferiority psychotherapy trials [83].

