Furthermore, following the procedures outlined by George and Mallery [84], General Linear Model Repeated Measures (GLM-RM) analyses will be conducted to examine longitudinal changes in major depressive disorder (MDD) and comorbid anxiety symptoms across assessment time points. The GLM-RM framework will be used to test the main effect of time, the main effect of treatment group (face-to-face vs. online EMDR), and the group × time interaction, which represents differential change over time between treatment modalities. Where significant effects are observed, planned post-hoc comparisons with Bonferroni correction [85] will be performed to examine changes in symptom severity between baseline (T01) and end of treatment (T04).

Finally, to account for repeated observations nested within individuals and to examine individual variability in symptom trajectories, hierarchical linear modeling (HLM) using maximum likelihood estimation will be employed, following the analytic guidelines described by Garson [86]. In these models, Level-1 will represent repeated symptom measurements over time, and Level-2 will represent individual participants. Time will be operationalized as the number of treatment sessions from baseline to follow-up and coded sequentially (e.g., 1, 2, 3, 4, 5…). Predictor variables will be entered as covariates and examined as fixed effects (representing average effects across participants) and, where appropriate, as random effects (representing individual variability in intercepts and slopes). Given the frequent co-occurrence of depressive and anxiety symptoms [87], reciprocal associations between depression and anxiety over time will be examined using HLM-based reciprocal association methodology [77, 80] and a 1–1–1 multilevel mediation modeling approach [88, 89].

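### Four therapists deliver all phase-three treatment, but neither the non-inferiority comparison nor the two-level model includes therapist, and the protocol does not commit each therapist to both arms

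*Protocol article*

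**What the plan says.** In the Protocol article, Study setting {9} describes phase three as a multi-centre trial in three cities, "where the adapted DeprEnd EMDR therapy protocol will be delivered by four EMDR certified therapists".

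Statistical methods {20a} sets out two relevant analyses:

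- **The decision analysis.** For the primary outcome, "non-inferiority is based on the between-group difference in change scores on the Hamilton Depression Rating Scale-17", baseline to end of treatment. The rule works by "comparing the estimated 95% confidence interval for the between-group difference to a pre-specified margin", which is 3 points. No model or covariates are named.
- **The trajectory model**, introduced last. Here "Level-1 will represent repeated symptom measurements over time, and Level-2 will represent individual participants". Predictors may enter as fixed effects or, where appropriate, "as random effects (representing individual variability in intercepts and slopes").

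Sequence generation {16a} minimizes on site, gender, baseline severity and comorbidity. Concealment mechanism {16b} lists age in place of site. Neither list contains therapist.

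Whether therapists work in both arms is not stated outright. Two sentences bear on it. Implementation {16c} has the system "automatically notify the treating therapist of the allocated intervention mode", and Who will be blinded {17a} says that "therapists will remain blind until after completing the initial consultation with clients".

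**The concern.** With 80 clients and four therapists, each therapist treats 20 on average. Clients of one therapist may have more similar outcomes than clients of different therapists. The protocol adopts a multilevel model to handle nesting, and it treats therapist performance as variable: fidelity is audited and competence is rated. Even so, no stated analysis carries therapist.

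The upper limit of one interval decides non-inferiority, so its width matters. The direction of any error depends on a fact the protocol leaves open. If each therapist treats in both modes (crossed), differences between therapists largely cancel from the arm comparison, and ignoring them wastes some precision. If therapists are tied to arms (nested), those differences are part of the arm comparison, and ignoring them makes the interval too narrow.

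**Working it through.** **Inputs from the protocol.** SD of change 8, 40 per arm, 1:1 allocation, margin 3, four therapists, two-sided 95% interval with only the upper limit tested (one-sided 0.025).

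**Assumptions.** The protocol gives no therapist variance, so 2–10% of total variance is assumed. Equal caseloads are assumed: 10 clients per therapist per arm if crossed, 20 per therapist if nested.

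**The plan's own figure.** (1.96 + 0.84)² × 2 × 64 / 25 = 7.84 × 128 / 25 = 40.1, and 80 / 0.85 = 94.1. The stated 40 per arm and 94 recruited are reproduced. No therapist design effect enters. The unadjusted half-width is 1.96 × 8 × √(2/40) = 3.51 points.

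**Crossed, therapist main effect only (share a of variance).** The main effect cancels from the arm difference, so the true variance is proportional to 1 − a. The within-arm sample variance still contains most of it. With four groups of 10 the expected value is (1 − a) + a × (40 − 10)/39 = (1 − a) + 0.769a. The width ratio is the square root of the second over the first.

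| a (assumed) | Width, unadjusted ÷ correct | One-sided error, 1 − Φ(1.96 × ratio) |
|---|---|---|
| 0.02 | √(0.9954/0.98) = 1.008 | 0.024 |
| 0.05 | √(0.9885/0.95) = 1.020 | 0.023 |
| 0.10 | √(0.9769/0.90) = 1.042 | 0.021 |

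Simulation with a true difference of 3 gives 0.025, 0.023 and 0.021. Adding therapist as a fixed effect returns the error to 0.025 in all three cases.

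**Nested, two therapists per arm.** Design effect = 1 + 19 × ICC. One-sided error of the unadjusted interval = 1 − Φ(1.96/√design effect).

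| ICC (assumed) | Design effect | One-sided error |
|---|---|---|
| 0.02 | 1.38 | 0.048 |
| 0.05 | 1.95 | 0.080 |
| 0.10 | 2.90 | 0.125 |

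Simulation gives 0.047, 0.080 and 0.128. A therapist fixed effect is no cure here. Intercept, arm and three therapist indicators make five columns of rank 4, so the arm effect cannot be estimated.

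**Crossed, with therapist-by-mode variation.** Take a 5% main effect and 2% therapist-by-mode variance, with the four therapists regarded as a random sample.

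- The true variance is proportional to 1 − 0.05 + 9 × 0.02 = 1.13.
- Unadjusted: the expected sample variance is 0.93 + 0.769 × 0.07 = 0.984. Then 1.96 × √(0.984/1.13) = 1.83, error about 0.034.
- With the therapist term: the residual variance is (72 × 0.93 + 3 × 1.13)/75 = 0.938. Then 1.96 × √(0.938/1.13) = 1.79, error about 0.037.

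Simulation agrees (0.033 and 0.036). At 5% therapist-by-mode variance it gives about 0.050 and 0.055. The fixed effect does not correct this component and slightly worsens it.

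**The case against.** The strongest case against the point is that it is silence and not error. Covariates for the primary comparison are commonly left to an analysis plan, and none is shown here. The two-level model could also take therapist as a fixed predictor without a third level. Both observations are correct. They limit the point to a modest addition, but they do not supply the missing commitment that each therapist treats both arms.

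A reader might infer more than the documents support, in four ways.

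- **That the client-level hierarchy produces the non-inferiority interval.** It does not. That model serves the trajectory analysis, and the interval comes from the change-score comparison.
- **That the interval is too narrow and false claims of non-inferiority are likely.** This needs nesting or appreciable therapist-by-mode variation. The notification and blinding sentences point to crossing, and minimizing on site, as {16a} specifies, works towards balanced arms within each clinic. With a main effect only, the planned interval errs slightly on the safe side.
- **That the nested error is 16%.** That doubles 0.080 for a two-sided test, whereas the rule uses only the upper limit. It also rests on an arrangement that the protocol's wording points away from.
- **That a therapist term cures a too-narrow interval.** Under nesting it cannot be fitted alongside arm, and under therapist-by-mode variation it does not help.

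In the other direction, crossing should not be treated as settled. It is inferred from two sentences, and therapist is not balanced by the minimization.

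**Conclusion.** The omission is real, and its likely effect is small. On the crossed reading that the protocol suggests, the unadjusted interval is about 1–4% too wide, and one-sided error is about 0.021–0.025 against 0.025. Including therapist would recover that precision and restore the nominal error rate. It would not remove a false-positive problem, because that reading with a main effect only has none.

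The larger risk is conditional. If therapists ended up mostly in one arm, one-sided error would be about 0.05–0.12, and no therapist covariate could mend it afterwards. The safeguard is a design commitment, which the protocol lacks.

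These sizes rest on assumed therapist variance of 2–10% and equal caseloads, neither of which the protocol states. The inflation from therapist-by-mode variation applies only if the aim is to generalize beyond these four therapists. A fixed-effect analysis is conditional on them.

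**What to change.** 1. State in Study setting {9} or Implementation {16c} that each of the four therapists treats clients in both arms, and record the treating therapist for every client before allocation is revealed.
2. In {20a}, include therapist as a four-level fixed effect in the primary HAM-D-17 change comparison and in the longitudinal model. With only four therapists, a fixed effect is more stable than a random variance.
3. Report arm differences by therapist descriptively. State that the fixed effect does not correct for therapist-by-mode variation and that inference is conditional on these four therapists.

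The cost is three degrees of freedom in the primary comparison (residual 75 instead of 78 with 80 clients), one sentence of design text and one descriptive table. Therapist identity is already known to the trial. The model should be fixed before unblinded outcome data are seen, which includes the planned efficacy interim at 60 participants.

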### Intervention description {11a}

This trial employs the evidence-based DeprEnd EMDR therapy protocol for depressive disorders [67]. This protocol is specifically optimized for depressive disorders through modifications in:History-taking (focused on depressive triggers vs. trauma),Preparation (enhanced psychoeducation on depression maintenance), andInstallation (targeting depressive cognition reprocessing) [21].

The DeprEnd EMDR therapy protocol has been culturally and methodologically adapted for the Pakistani context, and the full adaptation process has been published elsewhere [42]. In the present trial, both study arms follow the same adapted protocol, differing only in mode of delivery. The intervention will be delivered over 10–14 weekly sessions, depending on individual clinical presentation and treatment response. Each session will last approximately 60–90 min, consistent with standard EMDR therapy practice.In-person EMDR therapy will be delivered by EMDR-certified therapists in selected psychotherapy clinics. Sessions will follow the adapted DeprEnd EMDR protocol using standard face-to-face procedures, including therapist-guided bilateral stimulation and adherence to protocol fidelity requirements.Online EMDR therapy will be delivered via the BilateralBase platform, a validated telehealth system developed in the UK [68]. Therapists and clients will connect synchronously via secure video conferencing using a computer or mobile device. The platform provides visual and auditory bilateral stimulation, real-time therapist guidance, and session structuring consistent with in-person EMDR delivery. Session recordings are enabled for fidelity monitoring, with appropriate consent and ethical safeguards. Apart from delivery modality, the content, session structure, and therapeutic procedures remain equivalent to those used in the in-person arm.

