### Provisions for post-trial care {30}

All trial participants will have access to appropriate post-trial care based on their clinical needs. For responders to therapy (defined as ≥ 60% reduction in HAM-D-17 scores), follow-up sessions will be offered to consolidate treatment gains, consisting of two monthly booster EMDR sessions (in-person or online, per their assigned study arm). Non-responding patients will be referred to stepped-care options, including medication management or alternative evidence-based psychotherapies, such as Cognitive Behavioral Therapy, through the network of collaborating psychiatric clinics.

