### Outcomes {12}

#### Primary outcome

The primary outcome of the study is to study the change in depressive symptom severity. It will be assessed by using the Hamilton Depression Rating Scale-17 [69]. Depression assessments will be conducted at baseline (T01), mid-treatment (T02), end-of-treatment (T03), and follow-up (T04). The primary endpoint for evaluating clinical effectiveness and non-inferiority is the change in depression scores from baseline (T01) to end-of-treatment (T03).

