## Data collection and management

### Plans for assessment and collection of outcomes {18a}

Primary outcomes (depression severity assessed) and secondary outcomes (anxiety symptoms measured) will be collected at four timepoints: baseline (T1), mid-therapy (T2), post-intervention (T3), and 2-month follow-up (T4). All clinical ratings will be administered by trained research assistants who are blinded to treatment allocation. The feasibility and acceptability of the online platform will be evaluated using three validated instruments, as outlined in the protocol. Treatment fidelity and therapist competence will be assessed through both qualitative and quantitative methods, also detailed in the protocol. Data integrity will be ensured through automated checks for missing values and outliers, complemented by audits conducted by the statistical analyst. Any discrepancies will prompt source document verification by an independent monitor or research assistant.

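### The supporting longitudinal analyses mis-specify time: the post-hoc contrast labels end of treatment T04, and HLM time is a session count that depends on treatment response

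*Protocol article*

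**What the plan says.** All references are to the Protocol article.

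**Visit labels.** The Primary outcome section lists, after baseline, "mid-treatment (T02), end-of-treatment (T03), and follow-up (T04". It sets the primary endpoint as "change in depression scores from baseline (T01) to end-of-treatment (T03". Plans for assessment and collection of outcomes {18a} agrees, naming "post-intervention (T3), and 2-month follow-up (T4". Section {20a} also uses T1 to T3 for the non-inferiority comparison. Later in {20a}, however, the Bonferroni-corrected post-hoc comparisons after the repeated-measures general linear model (GLM-RM) are to examine "changes in symptom severity between baseline (T01) and end of treatment (T04".

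**Time in the HLM.** Section {20a} states that "Level-1 will represent repeated symptom measurements over time", with participants at Level 2. It then fixes the time variable: "Time will be operationalized as the number of treatment sessions from baseline to follow-up and coded sequentially", with 1, 2, 3, 4, 5 and so on as the example.

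**Length of the course.** Intervention description {11a} gives "10–14 weekly sessions, depending on individual clinical presentation and treatment response".

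**Care after treatment.** Provisions for post-trial care {30} offers responders "two monthly booster EMDR sessions" and refers non-responders to other care. The ancillary care section {34} repeats this. Neither section says when this care starts relative to T04.

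**The concern.** These are stated rules, not details left for an analysis plan, and they conflict with the design described elsewhere in the article.

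The contrast can be read as T01–T03 or as T01–T04. These are different estimands about two months apart. Leaving the label as it is leaves the visit open to choice after the data have been seen. If post-trial boosters or referrals begin before T04, a T04 contrast would also include care that depends on response.

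A session-count axis has two problems. First, it does not match the measurement occasions: there are four ratings, not one per session. Second, session number is determined after randomisation and partly by the outcome, so a per-session slope mixes the amount of improvement with the number of sessions given. If the two modes needed different numbers of sessions, the arm-by-time term would differ from zero even with identical improvement. The depression–anxiety models built on the HLM, for hypothesis (iv), would inherit the same axis.

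**Working it through.** The article gives no figure for this point, so there is nothing to reproduce. The check compares the labels and then places the visits on the competing time axes.

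**Step 1: labels.** The Primary outcome section, {18a} and the non-inferiority paragraph of {20a} all put end of treatment at T03. Only the post-hoc sentence in {20a} puts it at T04. The two cannot both hold.

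**Step 2: visits on each axis.** From the article: 10 to 14 weekly sessions, four visits, T04 two months after T03. Assumed: no missed weeks, and T02 at the halfway session. Two months = 2 × 365.25 / 12 / 7 = 8.7 weeks.

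| Axis | 10 sessions: T01, T02, T03, T04 | 14 sessions: T01, T02, T03, T04 |
|---|---|---|
| Weeks since baseline | 0, 5, 10, 18.7 | 0, 7, 14, 22.7 |
| Sessions, no boosters | 0, 5, 10, 10 | 0, 7, 14, 14 |
| Sessions, both boosters before T04 | 0, 5, 10, 12 | 0, 7, 14, 16 |
| Visit index | 1, 2, 3, 4 | 1, 2, 3, 4 |

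On the session axis the 8.7-week gap counts as 0 units without boosters and up to 2 with them. Boosters are for responders only, so the position of T04 would itself depend on response.

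**Step 3: slope for two clients.** Assume an illustrative fall of 12 points from T01 to T03.
- 10 sessions: −12 / 10 = −1.20 per session.
- 14 sessions: −12 / 14 = −0.86 per session.
- Ratio: 14 / 10 = 1.40, with the same improvement.

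**Step 4: slope for two arms.** Assume mean counts of 11 and 13 sessions and the same 12-point fall in both arms.
- −12 / 11 = −1.09 and −12 / 13 = −0.92.
- Difference: 0.17 points per session, a ratio of 13 / 11 = 1.18. As a statement about how much the arms improved, this difference is spurious.

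**Step 5: what weeks would do.** With strictly weekly sessions, week and session number coincide up to T03, so a straight T01–T03 slope in weeks is also −1.20 and −0.86. Weeks place T04 correctly and give the slope a real meaning (rate per week). Only visit as a category compares the amount of change at T03 directly, and in this illustration it gives no difference.

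**The case against.** The strongest reply is that this is one mistaken label and one loosely worded sentence in supporting analyses. Much of it stands.

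- A reader might infer that hypothesis (iii) is tested at the wrong visit. The article does not support that. The hypothesis predicts reduction over time and names no visit, and the GLM-RM tests of time, group and their interaction use the assessment time points. T04 appears only in the post-hoc comparison, where the words still say end of treatment, so a slip is the likeliest reading. It still needs correcting, because it sits in a planned contrast.
- A reader might infer that the follow-up cannot be placed at all. That is too strong. Coding in sequence could mean a visit index, which gives T04 a position, and a responder who takes boosters has further sessions to count. But an index is not what the sentence defines, the example runs past four, and intervals of 5–7, 5–7 and 8.7 weeks would be treated as equal.
- The booster argument depends on timing that the article does not give. It is conditional.
- The ratio of 1.40 compares two individuals at the extremes, not two arms. The article gives no expected session count by arm, and {11a} keeps content and structure equivalent. The arm-level figure rests on the assumed 11 and 13.
- A reader might also infer that a response-dependent course length moves T03 and so favours non-inferiority. That is a separate matter. It would need one arm to respond more slowly and receive more sessions, which the article does not show, and measuring the outcome at the end of an individually tailored course is a legitimate choice.

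**Conclusion.** Two defects hold. The end-of-treatment label in the post-hoc contrast contradicts the visit definitions used everywhere else that matters for the endpoint. The HLM time variable is a response-dependent session count that matches neither the four measurement occasions nor the interval to follow-up.

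The reach is limited to the GLM-RM post-hoc contrasts and the HLM-based analyses for hypotheses (iii) and (iv). The primary T1–T3 non-inferiority comparison does not use either element and is unaffected.

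The size is illustrative: 0.17 points per session between arms with equal improvement, if mean counts were 11 and 13 and the fall was 12 points. With equal session counts in the two arms this arm-level difference disappears, but the misplacement of T04 remains. Confidence is high on the two textual defects. The size in this trial cannot be known from the article.

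**What to change.** 1. In {20a}, name the end-of-treatment contrast as T01 versus T03, in line with the Primary outcome section. Report T01 versus T04 as a separate follow-up contrast, and state whether post-trial boosters or referrals can begin before T04.
2. Define HLM time as scheduled visit (T01–T04, categorical) or as actual weeks since baseline or randomisation. Visit is the safer choice for comparing the amount of change between arms. If weeks are used, the arm-by-time term of a straight line should be read as a difference in weekly rate, since T03 falls at the end of a course of varying length.
3. Keep session count as a descriptive result by arm, or within the exploratory dose–response analysis under Additional analyses {20b}.

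The cost is analysis wording. Using weeks also needs the date of each assessment; the article does not say whether these are recorded. The visit schedule and the primary endpoint stay as they are.

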## Hypotheses of study

Since the second phase of this study deals with clinical effectiveness, the following directional hypotheses will be tested:i.The adapted EMDR therapy will demonstrate a high level of feasibility, usability, acceptance, technical operability, and safety when delivered through in-person and online modes.ii.The online delivery of the adapted EMDR therapy is non-inferior to the in-person mode for treating major depressive disorder in Pakistaniii.The adapted EMDR therapy will bring about significant temporal reduction in the major depressive disorder symptoms across in-person and online modes.iv.The major depressive disorder symptoms are reciprocally linked to the comorbid generalized anxiety disorder symptoms in a manner that treatment conditions moderate this relationship.

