## Methodology on treatment fidelity

Treatment fidelity will be established both qualitatively and quantitatively by adhering to the recommendations outlined by Dorsey et al. [76]:The psychotherapy sessions will be video recorded and reviewed by two EMDR therapy experts. Moreover, quantitative ratings of recorded sessions will be done by using predefined rating scales such as the EMDR Fidelity Rating Scale [77].The therapist’s competence will be assessed by self-reported rating scales such as the Instrument for Assessing Therapist Competence in Global Mental Health [78].Finally, patients’ satisfaction and perception about adapted DeprEnd EMDR therapy protocol will be assessed by Scale for Patient Experience of Online EMDR therapy [79] and Satisfaction with Therapy Scale [80].

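### The reciprocity part of hypothesis (iv) has no fixed time order: fitted to same-visit scores, the named 1-1-1 mediation cannot tell reciprocal influence from depression and anxiety improving together

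*Protocol article*

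**What the plan says.** Protocol article, Hypotheses of study, item (iv): "The major depressive disorder symptoms are reciprocally linked to the comorbid generalized anxiety disorder symptoms in a manner that treatment conditions moderate this relationship". This has two parts, a reciprocal link and moderation of that link by arm.

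Statistical methods for primary and secondary outcomes {20a}: "reciprocal associations between depression and anxiety over time will be examined", and the methods are given as "using HLM-based reciprocal association methodology [77, 80] and a 1–1–1 multilevel mediation modeling approach". In the hierarchical models of that section, level 1 is the repeated symptom measurement and level 2 the client. For time, "Time will be operationalized as the number of treatment sessions from baseline to follow-up and coded sequentially". The section gives no lag, no order of predictor, mediator and outcome, and no rule for declaring reciprocity.

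Primary outcome: "Depression assessments will be conducted at baseline (T01), mid-treatment (T02), end-of-treatment (T03), and follow-up (T04". Secondary outcomes lists the same four occasions for anxiety. Plans for assessment and collection of outcomes {18a} confirms that both "will be collected at four timepoints: baseline (T1), mid-therapy (T2), post-intervention (T3), and 2-month follow-up (T4".

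Methodology on treatment fidelity attaches the first of the two method citations to the "EMDR Fidelity Rating Scale [77", and attaches reference 80 to a scale of satisfaction with therapy.

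**The concern.** Reciprocity is a statement about two directions over time. A 1-1-1 mediation is a single one-way chain whose three variables are all measured at level 1. On scores from the same visit, the path between anxiety and depression is a concurrent association, and such an association has no direction. Exchanging mediator and outcome returns the same evidence, so significance in both directions adds nothing to significance in one.

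Two correlated symptoms that both fall during treatment can therefore produce an apparent two-way mechanism when neither affects the other. The second named method might avoid this, but it cannot be identified, because its two references point elsewhere in the article to rating scales. At stake is the reciprocity component of one of the four listed hypotheses.

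**Working it through.** **The plan's own figures.** The sample size section gives n = (1.96 + 0.84)² × 2 × 8² / 5² = 7.84 × 128 / 25 = 40.14, taken as 40 per arm and 80 in total; 80 / 0.85 = 94.1, taken as 94 recruited. Both reproduce. The article gives no effect size, power or error rate for hypothesis (iv), so N = 80 and four visits are the only inputs it supplies.

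**Why the two directions are one test.** Remove each client's mean and the time effect from both symptoms. What remains is a partial correlation r with df = 80 × (4 − 1) − 2 = 238. The test of the path is t = r × √(df / (1 − r²)). This is unchanged when depression and anxiety swap places. In simulation the two t-statistics were identical in every run. This holds whatever the size of r.

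**How easily that test is positive.** The noncentrality is r / √(1 − r²) × √238:
- r = 0.1: 1.55, power 34%
- r = 0.2: 3.15, power 88%
- r = 0.3: 4.85, power 99.8%

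**Simulation with no influence in either direction.** 80 clients, four visits, person-mean-centred same-visit models with linear time, two-sided 5%. Assumptions not in the documents: visit residual SDs of 5 (depression) and 3.5 (anxiety), declines of 12 and 6 points, and person-specific slopes independent between symptoms. The within-person residual correlation is also assumed. Entries are the share of trials with both directions significant.

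| Residual correlation | 0 | 0.1 | 0.2 | 0.3 |
|---|---|---|---|---|
| Linear course, 1,500 runs | 5.7% | 26.0% | 79.1% | 98.3% |
| Linear course, repeat | 6% | 27% | 79% | 99% |
| Early gain then plateau, 1,500 runs | 34.3% | 80.3% | 98.2% | 100% |
| Early gain then plateau, repeat | 33% | 79% | 98% | 100% |

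- The plateau rows are higher because a straight line in time leaves the shared curve of the two means in the residuals. A plateau is plausible here, since T4 is two months after treatment ends.
- With time omitted, both directions were significant in 100% of runs in every setting.
- With residual correlation 0 but slopes correlated 0.5, the rate was 16% (linear course) or 68% (plateau).
- Testing the indirect effect from time through mediator to outcome with a Sobel test gave nearly the same rates (5.5%, 25%, 78% and 98% for the linear course).
- Visit-specific means do not cure the problem. A separate simulation with categorical time and person-mean centring gave 99% when intercept, slope and same-visit correlations were 0.5, 0.5 and 0.3, and 86% at 0.3, 0.3 and 0.2.

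**Moderation by arm.** With no true moderation, the arm-by-mediator interaction was rejected in 4–6% of runs. Both directions significant together with moderation in either direction occurred in about 0.6–10%.

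**Lagged alternatives, again with no true cross-effect.**
- Random-intercept cross-lagged model, both lagged paths required: 0–0.4% without slope variation, and 2.9% with correlated slopes left unmodelled. A single path then reached 11–15%, which is why both are needed. A second simulation gave 1.3% and 2.0%.
- Power of that model was 79% when both true lagged effects were 0.3 and slopes did not vary.
- Pooled lagged regression without person effects: both paths falsely significant in 0.2–46% of four-visit settings, so a lag alone is not sufficient.

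**The case against.** The strongest reply is that the article never says the models use same-visit scores. It speaks of associations over time, a lagged score is also a level-1 variable, and shared visits do not prevent lagging. An article may leave lag, centring and variable order to the analysis plan. All of this stands, so the same-visit fit is an inference, and a bare complaint that details are missing would be no finding. What remains is that the article fixes a named method which, in its usual same-occasion form, cannot bear the claim.

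Reference numbers also drift elsewhere: the adaptation paper is 42 in some sections and 54 in others, and 84 serves both as a statistics guide and as support for rural access. The wrong citation therefore shows only that the intended source is unknown. It does not show that no lagged method was meant.

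A reader might infer that the plan's null is the absence of same-visit association and that hypothesis (iv) will be confirmed whatever the truth. The documents do not support this. They state no null, and they say the symptoms are linked, which is weaker than saying that each drives the other. With time adjusted, a linear course and no shared variation, the rate stays near 5%. The moderation part keeps its nominal error, so the full hypothesis is not confirmed automatically. A significant moderation result would, however, still describe a same-visit association.

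**Conclusion.** The concern holds for the reciprocity component of hypothesis (iv), on the condition that same-visit scores are analysed. Under that condition the symmetry of the two directions is exact for the person-mean-centred model and needs no assumption about correlations. The size of the false-claim risk does need one. The range runs from about 6% at zero residual correlation with a linear course to 98–100% at 0.3, and from about 33% upward if improvement plateaus while time is modelled as a straight line. The article expects the two symptoms to occur together often but gives no correlation, so the 0 to 0.3 range is assumed.

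This is a secondary analysis. The arm-moderation test keeps about 5% error, and the primary non-inferiority comparison does not depend on any of it.

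**What to change.** 1. Report any same-visit 1-1-1 result as concurrent association between depression and anxiety, with no statement about direction.
2. Base a reciprocity claim on within-person lagged paths over T1 to T4, for example a random-intercept cross-lagged model with visit-specific means and same-visit residual correlation. Add a sensitivity analysis allowing person-specific slopes.
3. Claim reciprocity only if the 95% confidence intervals of both lagged paths, anxiety to later depression and depression to later anxiety, exclude zero.
4. Report the difference between arms in those paths with a confidence interval, as the test of the moderation part.
5. Label the analysis exploratory and replace references 77 and 80 with the source of the intended method.

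The data are already planned, so the cost is wording and modest modelling work. The price is power: the 79% figure assumes lagged effects of 0.3 each way and no slope variation, and four visits on 80 clients may leave the slope model poorly determined. Hypothesis (iv) may then go unsupported.
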